### Calculation of sample size

The sample size was calculated based on a previous study [28], in which a similar experimental model and exercise protocol was employed as that to be used in the proposed study. The sample size calculation considered a β of 20% and α of 5%. In the study used as reference for this calculation of Baroni *et al*. [28], LLLT led to the post-exercise recovery of creatine kinase (CK) (muscle injury marker) to 435.95 U/l (standard deviation: 238.04), whereas placebo treatment led to an increase in CK to 1,327.58 ± 949.82 U/l. Using these parameters, a total of seven volunteers would be needed for each of the four groups in each phase of the study (total of 28 volunteers per phase).

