#### Isokinetic protocol: maximum voluntary contraction (MVC)

An isometric dynamometer will be used for the evaluation of muscle function and the execution of the exercise protocol. This instrument is considered the method with the greatest reliability for the measure of the musculoskeletal performance. Immediately after the stretching and warm-up exercises, the maximum voluntary contraction (MVC) test will be performed. For such, the volunteers will sit on the seat of the isokinetic dynamometer (System 4, Biodex Medical Systems, Inc., Shirley, NY, USA) with an angle of 100° between the trunk and hip and the non-dominant leg positioned with the knee at 60° of flexion (0° corresponds to complete knee extension) and attached to the seat of the dynamometer by a strap. The dominant leg will be positioned at 100° of hip flexion and will also be attached to the seat by a strap. The volunteers will also be attached to the seat of the dynamometer through the use of two straps crossing the trunk. The volunteers will be instructed to cross their arms over the trunk and the axis of the dynamometer will be positioned parallel to the center of the knee. The MVC test will consist of three 5-second isometric contractions of the knee extensors of the non-dominant leg. The highest torque value of the three contractions (peak torque) will be used for the statistical analysis. The choice of this parameter is due to the fact that this variable reflects the maximum generation of force by the muscle. Instructions on how to execute the test will be given first and the volunteers will receive verbal encouragement during the execution of the test. This test has demonstrated reliability and reproducibility in a previous study carried out [28]. The MVC will be performed immediately (1 minute) after the eccentric contraction protocol as well as 1, 24, 48, 72 and 96 hours after the eccentric contraction protocol to evaluate post-exercise muscle recovery.

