### Data analysis

The intention-to-treat analysis will be followed. The primary outcome will be peak torque obtained from MVC at different time-points. Secondary outcomes will be biochemical markers CK, LDH, IL-1β, IL-6, TNF-α, TBARS, carbonylated proteins, CAT and SOD.

Data will be expressed as mean and standard deviation and will be firstly tested regarding normal distribution using Shapiro–Wilk test. ANOVA test with repeated measurements for the time factor will be performed to test between-groups differences (followed by the Bonferroni post hoc test). The level of significance for the statistical analysis will be set at 5% (*P* ≤0.05).

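### The primary MVC analysis is an unadjusted repeated-measures ANOVA with no named primary contrast; adjusting for a pre-laser MVC would gain modest to large power at 7 per group

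*Protocol article*

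**What the plan says.** - **Outcome.** Data analysis: "The primary outcome will be peak torque obtained from MVC at different time-points". No time point, summary measure or contrast is singled out.
- **Method.** Same section: "ANOVA test with repeated measurements for the time factor will be performed to test between-groups differences", "followed by the Bonferroni post hoc test". No baseline covariate is named, and the Bonferroni family is not defined.
- **Measurements.** The section on the MVC test has one test after warm-up and before the eccentric exercise, and then: "The MVC will be performed immediately (1 minute) after the eccentric contraction protocol as well as 1, 24, 48, 72 and 96 hours". That is one pre-exercise and six post-exercise values, unevenly spaced.
- **Sample size.** "a total of seven volunteers would be needed for each of the four groups in each phase of the study". This rests on creatine kinase (CK), which Data analysis lists as a secondary outcome. No SD, effect size or within-athlete correlation is given for MVC.
- **Order of laser and first MVC.** The Abstract (Design and methods) places the MVC-based test before the laser. The section on variation of dose (phase 1) places the laser 2 minutes before the pre-exercise MVC test.

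**The concern.** Athletes differ in strength, and an athlete's pre-exercise torque is likely to predict his later torque. With 28 athletes in four groups, an analysis that does not use this carries the stable differences as noise. The method named offers two tests that could answer the question, and neither uses the pre-exercise value efficiently. The group main effect compares athlete averages, so stable differences stay in its error. The group-by-time test removes them but spreads a sustained effect over many degrees of freedom.

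Phase 2 uses whichever dose did best in phase 1, so an imprecise phase 1 comparison carries into the second half of the trial. With no primary contrast named, it is also open which F test, or which of the pairwise comparisons at various times, is the primary result.

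**Working it through.** **The plan's own figure.** The CK inputs are "to 435.95 U/l (standard deviation: 238.04") and "placebo treatment led to an increase in CK to 1,327.58 ± 949.82 U/l".

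- Difference: 1,327.58 − 435.95 = 891.63.
- Simple average of the two SDs: 593.93. Then n = 2 × (1.960 + 0.842)² × (593.93/891.63)² = 6.97, so 7 per group.
- Root-mean-square SD: 692.39. The same formula gives 9.47, so 10.

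The stated 7 is reproduced under the first choice. It says nothing about power for MVC.

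**Set-up for MVC.** From the documents: 4 groups × 7, one pre-exercise and six post-exercise values, α 5%. Assumed: unit SD at each time, one group better by 0.75 SD at all six post-exercise times and none before, and a pre-exercise value taken before the laser. For the repeated-measures ANOVA the pre-exercise value is taken as a level of time, giving 3 × 6 = 18 numerator degrees of freedom. Without it there would be 3 × 5 = 15.

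The effect sum of squares is 7 × 0.75² × (1 − 1/4) = 2.953. Noncentrality is 2.953 divided by a variance factor, which under equal correlation ρ is:

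- group main effect: [(1 + 6ρ)/7] / (6/7)², on 3 and 24 df
- group-by-time: (1 − ρ) × 7/6, on 18 and 144 df
- ANCOVA of the post-exercise mean on the pre-laser value: (1 + 5ρ)/6 − ρ², on 3 and 23 df

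| Equal ρ | Variance factors (main / group-by-time / ANCOVA) | Noncentrality | Power |
|---|---|---|---|
| 0.5 | 0.778 / 0.583 / 0.333 | 3.80 / 5.06 / 8.86 | 29 / 19 / 60% |
| 0.8 | 1.128 / 0.233 / 0.193 | 2.62 / 12.66 / 15.27 | 21 / 49 / 85% |
| 0.9 | 1.244 / 0.117 / 0.107 | 2.37 / 25.31 / 27.69 | 19 / 86 / 99% |

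At 0.5 and 0.8 the ANCOVA power is from simulation, which allows for chance imbalance in the covariate. The noncentral F without that allowance gives 62% and 87%. Simulating all three tests gives 28/20/60% and 20/48/85%, within two points of the table.

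**Decaying correlation.** Under AR(1) 0.8, indexed by measurement order, simulated power is about 27% (main), 14% (group-by-time, Greenhouse-Geisser-corrected) and 47% (ANCOVA). At AR(1) 0.6 the main effect has 38% against 50% for ANCOVA.

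**Late effect only** (0.75 SD at 48, 72 and 96 h).

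- Equal ρ 0.8: ANCOVA on the mean of all six post-exercise values has 29% power, against 83% for the corrected group-by-time test. ANCOVA on the mean of the three late values has 78%.
- AR(1) 0.8: ANCOVA on the six-value mean has 14–16% and the corrected group-by-time test 28%. ANCOVA on the three late values has 29%.

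**If the pre-exercise MVC already carries the effect.** At equal ρ 0.8, with the 0.75 SD difference also present at that test, ANCOVA power falls to 7–8%, against about 28% for the group main effect.

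**The case against.** Several stronger readings are tempting, and the article does not support them.

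- **That the plan enters baseline as a level of time.** This is the natural reading, but it is not written. The point survives without it: whether or not the pre-exercise value is a level, the main effect is not adjusted for it.
- **That most of the power is thrown away.** The loss depends on an unstated correlation and on which F test is read. At equal correlation 0.9 the group-by-time test has 86% against 99%; at AR(1) 0.6 the main effect keeps about three quarters of the adjusted power (38/50).
- **That the type I error is inflated.** Under AR(1) 0.6 to 0.9 an uncorrected group-by-time test rejects a true null in about 8–12% of trials, but the article does not say that it is uncorrected. A correction is commonly left to the analysis plan and brings the rate to about 4–6%. The group main effect does not need sphericity.
- **That the post hoc tests number 36.** Six pairs × six post-exercise times gives 36, but the Bonferroni family is undefined, so this is only a possible count.

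Two further objections stand and limit the remedy. An overall post-exercise mean is not always the better target: for a late effect it loses clearly to the group-by-time test. And under the order given in the section on variation of dose there is no pre-laser MVC, so adjusting for the test actually done could remove much of the effect.

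It can also be said that covariates are a matter for the full analysis plan. But the article does not stay silent on method. It fixes one, and that method as described is unadjusted.

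**Conclusion.** The point holds in limited form. As stated, the primary analysis does not adjust for pre-exercise MVC and names no primary contrast. For a sustained effect, adjustment for a true pre-laser value gave more power than either F test in every scenario tried, by an amount from modest to large.

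The size rests on an assumed effect of 0.75 SD in one group, assumed correlations, and a covariate measured before irradiation. The advantage of the overall mean also requires an effect present across the post-exercise period. For a late effect, adjustment at the late times performs about as well as the corrected group-by-time test (78% against 83%, and 29% against 28%), so the time point or summary matters as much as the covariate. The contradiction over the order of laser and MVC has to be settled before any of this can be used.

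**What to change.** 1. Reconcile the Abstract with the section on variation of dose, and state whether the pre-exercise MVC is taken before or after irradiation.
2. If a pre-laser MVC exists, replace the stated test with a baseline-adjusted analysis of the post-exercise values: ANCOVA, or a mixed model with pre-laser MVC as covariate plus group, time and group-by-time.
3. Name one primary time point or summary, and active-versus-placebo contrasts. Whether this is the overall post-exercise mean or a particular recovery time is the investigators' choice of estimand. Make it before the data are seen, noting that the mean is weaker if the effect appears only late.
4. Treat CK and the other markers in the same way, using their pre-exercise values, provided those samples are drawn before the laser.
5. If a repeated-measures F test is kept, state a sphericity correction for the group-by-time test.

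The cost is one degree of freedom and revised analysis wording. No new data are needed if the MVC precedes the laser, as the Abstract states. If it does not, the covariate is not available as the study is described, and adjusting for the post-laser MVC should not be substituted.

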### Composition of groups and randomization process

The volunteers will be randomly allocated to four experimental groups (n = 7 per group) based on the LLLT dose (phase 1) and power (phase 2) (Figure 1). Randomization will be carried out by a simple drawing of lots (A, B, C or D). The laser unit will emit the same sound regardless of the programmed power output. Randomization labels will be created using a randomization table at a central office, where a series of sealed, opaque, numbered envelopes will be used to ensure confidentiality. Randomization will be conducted by a participating researcher, who will have the function of programming the laser device based on the randomization results. This researcher will be instructed not to inform the participants or other researchers regarding the LLLT dose (phase 1) or power (phase 2) until the study has been completed. Thus, the researcher in charge of the administration of the LLLT will be blinded to the dose and power applied to the volunteers.

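### Holm could replace the planned Bonferroni post hoc test with the same error control and a small gain in power, as could Tukey if the family is only the six group pairs

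*Protocol article*

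**What the plan says.** The Data analysis section states: "The primary outcome will be peak torque obtained from MVC at different time-points". Between-group differences are tested by ANOVA with repeated measures over time, "followed by the Bonferroni post hoc test", at a 5% significance level. The section does not say which comparisons the Bonferroni correction covers.

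Under Calculation of sample size, the article concludes that "a total of seven volunteers would be needed for each of the four groups in each phase of the study". That figure rests on one contrast between laser and placebo in creatine kinase (CK), with α of 5% and β of 20%. The reference values are 435.95 U/l (SD 238.04) with laser, while "placebo treatment led to an increase in CK to 1,327.58 ± 949.82 U/l". No effect size or SD is given for peak torque.

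The isokinetic MVC section lists six post-exercise measurements: 1 minute, then 1, 24, 48, 72 and 96 hours. The section on variation of power carries the best phase 1 dose into phase 2, so comparisons between active doses matter as well as those with placebo.

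**The concern.** Four groups give six pairs. With seven athletes per group, the post hoc step decides whether a dose is declared better than placebo or than another dose, and there is little power to spare. Plain Bonferroni does not use the whole 5% when the comparisons share groups and are therefore correlated. Other procedures use more of it on the same comparisons. What is at stake is a modest amount of power that could be had without more athletes, more data or different comparisons.

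**Working it through.** **1. The article's own figure.** The CK difference is 1,327.58 − 435.95 = 891.63 U/l. The simple average of the two SDs is (238.04 + 949.82)/2 = 593.93. For a two-sided 5% test with 80% power, n = 2 × (1.960 + 0.842)² × (593.93/891.63)² ≈ 6.97, so 7 per group. The stated size is reproduced, with no allowance for multiple comparisons. With the root-mean-square SD, √[(238.04² + 949.82²)/2] = 692.39, the same formula gives 10.

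**2. Set-up for the comparison.** Groups: 4 of 7. Pairs: 4 × 3/2 = 6. Between-group error degrees of freedom: 28 − 4 = 24. Assumed effect: 891.63/692.39 = 1.29 SD, with equal SDs in all groups. This describes one between-group contrast, such as a single value or time average per athlete, and not the full repeated-measures model.

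**3. Critical values for |t|.**
- Bonferroni: t(1 − 0.05/12; 24) = 2.875
- Tukey: q(0.95; 4, 24)/√2 = 2.759
- Holm: orders the six p-values and compares them in turn with 0.05/6, 0.05/5, 0.05/4, 0.05/3, 0.05/2 and 0.05, stopping at the first failure

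Multiplied by √(2/7) = 0.5345, the smallest observed difference that reaches significance is 1.54 SD (Bonferroni) or 1.47 SD (Tukey). Holm's first step is the Bonferroni step, and its later thresholds are more lenient. So it can never reject less, and it can never raise the chance of at least one rejection.

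**4. Error and power.** Power for one pair comes from the noncentral t with noncentrality 1.29 × √(7/2) = 2.41. Holm, the family-wise error and the chance of at least one true difference come from simulation.

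| | Bonferroni | Holm | Tukey |
|---|---|---|---|
| Family-wise error, all groups equal | 3.9% | 3.9% | 5.0% |
| Power per true pair, all doses 1.29 SD from placebo | 34% | 37% | 38% |
| At least one true difference, same pattern | 57% | 57% | 61% |

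Holm's gain depends on the pattern of means. With two groups halfway between the extremes, its power for the 1.29 SD pair is 35%.

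**5. Other effect sizes (Bonferroni v Tukey, per pair).** With the averaged SD (1.50 SD): 48.7% v 53.0%. With the placebo SD (0.94 SD): 15.7% v 18.3%. The group size for 80% power on one pair is 16 v 15 at 1.29 SD, 12 v 12 at 1.50 SD and 29 v 28 at 0.94 SD.

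**6. If pairs are compared at each time-point.** The family becomes 6 × 6 = 36. Holm extends to it directly. A six-pair Tukey at each time does not hold 5% across times: were the times independent, the error would be 1 − 0.95⁶ = 26%, and it is less with correlation.

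**7. Unequal variances.** Take the CK SDs, with three groups at 238.04 and placebo at 949.82. The pooled variance is (3 × 238.04² + 949.82²)/4 ≈ 268,037, so the pooled standard error of a difference is √(2 × 268,037/7) ≈ 277. The true value for dose versus placebo is √[(238.04² + 949.82²)/7] ≈ 370. Simulated family-wise error with equal means is about 9% for Bonferroni and Holm and 10% for Tukey.

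**The case against.** The strongest reply is that Bonferroni is a recognised procedure, fixed in advance, that controls the 5% level under the usual assumptions, and that nothing in the article contradicts its use. That stands. A reader might infer that the plan is wrong, but the documents support only that it can be improved.

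Second, the six-pair family is an assumption. The article names no family, and its repeated measurements allow pairs at each time. This also stands, and it limits Tukey to the case where only six pairs are compared. It does not touch Holm, which improves on Bonferroni whatever the family.

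Third, a reader might infer that the swap restores the planned power. It does not. At 1.29 SD an unadjusted comparison with 24 degrees of freedom has about 64% power. Adjustment for six pairs takes this to 34%, and Tukey returns 4 points. Most of the shortfall comes from sizing on one unadjusted CK contrast, a secondary outcome. Nothing can be computed for peak torque.

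Fourth, one might hope to deal with the CK variances by using Holm-adjusted Welch tests whenever variances look different. With seven per group and no criterion, that chooses the test after seeing the data. It also costs power: in simulation at the CK means and SDs, the chance of at least one true difference is about 27%, against about 68% for pooled Bonferroni. Part of that loss buys validity, since pooled tests exceed 5% there.

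**Conclusion.** A cheap improvement, not a correction of an error. Holm's advantage over Bonferroni holds for any fixed family and needs no further assumption. Tukey's needs the six-pair family, equal group sizes and similar variances. At the assumed 1.29 SD the gain is about 3 points per true pair with Holm (1 to 3 over the patterns examined) and about 4 with Tukey. It is worth at most one athlete per group. Only Tukey raises the chance of finding anything at all. These sizes rest on CK figures with equal SDs and a single between-group contrast, so they are illustrative for the primary outcome. A reader might infer that the false-claim rate stays comfortably below 5% after the swap. That is not so: Tukey uses the full 5.0% when all groups are equal, and with variances as unequal as those of CK every pooled method goes above 5%.

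**What to change.** In Data analysis, replace the Bonferroni post hoc test with Holm-adjusted post hoc pairwise comparisons over the same family of comparisons, and name that family. If it is only the six group pairs on one between-group contrast, Tukey may be named instead. State for each outcome, before any data are seen, whether the tests use a pooled SD or are Welch tests. The cost is a phrase or two, with no new data, athletes or comparisons. The one drawback of Holm is that it has no simple simultaneous confidence intervals; Tukey does. Recruitment was under way when the article was submitted, so the change belongs in a dated amendment or the analysis plan before unblinding.

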## Discussion

In the proposed study, the ideal LLLT application dose and power will be identified and the long-term effects of LLLT on post-exercise muscle fatigue and musculoskeletal recovery will be evaluated. For such, evaluations will be carried out of peak torque during MVC, late-onset muscle pain will be determined and biochemical analyses will be performed to determine changes in markers of inflammation, oxidative stress and muscle damage. The inflammatory process is known to be a defensive reaction against injury. This process has been extensively studied in its different aspects. Briefly, the main inflammation events are: 1) tissue injury; 2) the release of vasoactive substances by the injured tissue; 3) vasodilatation; 4) leukocyte adherence; 5) the migration of leukocytes from the blood stream to the injury site; and 6) tissue repair. Thus, muscle inflammation is a natural consequence of exercise-induced muscle damage [30].

Over time, LLLT exhibits a biphasic, dose–response pattern. This means that intermediate doses within a ‘therapeutic window’ trigger stimulation effects in biological tissue, whereas doses outside this range do not trigger any effects [31-34]. However, the therapeutic window varies depending on the condition to be treated [31]. Likewise, the power and irradiation time employed are extremely important to obtaining the best results. Thus, a short irradiation time and an output power that is either too low or too high can lead to null results [31,34]. Our intention, therefore, is to determine ideal laser therapy application parameters capable of slowing down the physiological muscle fatigue process, reducing injuries or micro-injuries in skeletal muscle stemming from physical exertion and accelerating post-exercise muscle recovery. We believe that, unlike drug therapy, LLLT has a biphasic dose–response pattern.

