**Design and methods:**

A double-blind, randomized, placebo-controlled clinical trial with be conducted. After fulfilling the eligibility criteria, 28 high-performance athletes will be allocated to four groups of seven volunteers each. In phase 1, the laser power will be 200 mW and different doses will be tested: Group A (2 J), Group B (6 J), Group C (10 J) and Group D (0 J). In phase 2, the best dose obtained in phase 1 will be used with the same distribution of the volunteers, but with different powers: Group A (100 mW), Group B (200 mW), Group C (400 mW) and Group D (0 mW). The isokinetic test will be performed based on maximum voluntary contraction prior to the application of the laser and after the eccentric contraction protocol, which will also be performed using the isokinetic dynamometer. The following variables related to physical performance will be analyzed: peak torque/maximum voluntary contraction, delayed onset muscle soreness (algometer), biochemical markers of muscle damage, inflammation and oxidative stress.

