#### Variation of dose (phase 1)

In phase 1, the output power will be fixed at 200 mW and LLLT will be applied 2 minutes prior to the pre-exercise MVC test with the cluster in direct contact with the skin at six distinct sites of the knee extensor musculature of the non-dominant limb (two medial, two lateral and two central sites). As the cluster has five diodes and six different sites will be irradiated, a total of 30 points will be irradiated in the musculature. Based on the results of the randomization, the volunteers of the four experimental groups will receive the following doses: Group A, 2 J per diode, 10 J on each application of the cluster with 200 mW (10 seconds of irradiation at each site), 60 J of total irradiated energy on the muscle (60 seconds of total irradiation time); Group B, 6 J per diode, 30 J on each application of the cluster with 200 mW (30 seconds of irradiation at each site), 180 J of total irradiated energy on the muscle (180 seconds of total irradiation time); Group C, 10 J per diode, 50 J on each application of the cluster with 200 mW (50 seconds of irradiation at each site), 300 J of total irradiated energy on the muscle (300 seconds of total irradiation time); and Group D, 0 J per diode (placebo) (20 seconds of irradiation at each site, 120 seconds of total time, but without effective irradiation).

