#### Variation of power (phase 2)

The aim of phase 2 is to determine the best power/irradiation time (Watts/s) for use on humans to enhance muscle recovery following physical exercise. For such, the dose with the best results in phase 1 will be used and the same methodological and evaluative measures will be employed. Thus, only the power of the equipment (and consequently irradiation time) will be varied (100, 200, 400 or 0 mW). As energy (E) expressed in Joules is equal to power (P) expressed in Watts multiplied by time (t) measured in seconds, different power variations will lead to the same total energy delivered to the tissue. *A priori*, if the best dose were determined to be 10 J, the following would be the parameters:

•10 J = 0.1 W (100 mW) × 100 s

•10 J = 0.2 W (200 mW) × 50 s

•10 J = 0.4 W (400 mW) × 25 s

•10 J = 0.0 W (placebo, 60 s)

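### The protocol says the ideal dose and power will be identified, but doses are compared only at 200 mW and powers only at the one dose picked

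*Protocol article*

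**What the plan says.** The Discussion opens with an unqualified claim: "In the proposed study, the ideal LLLT application dose and power will be identified". The aim in the abstract is to find the best dose and the best power or irradiation time, and the title asks the same question. No section limits the answer to the settings tested.

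The design is sequential. Under Variation of dose (phase 1): "In phase 1, the output power will be fixed at 200 mW". The active doses there are 2, 6 and 10 J per diode, with a 0 J placebo group. Under Variation of power (phase 2), "the dose with the best results in phase 1 will be used", and "only the power of the equipment (and consequently irradiation time) will be varied (100, 200, 400 or 0 mW" mW). That section also states that energy equals power multiplied by time.

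Two remarks in the Discussion bear on the claim. On shape: "Over time, LLLT exhibits a biphasic, dose–response pattern". On delivery: "a short irradiation time and an output power that is either too low or too high can lead to null results".

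**The concern.** Varying one factor at a time gives two conditional answers: the best dose at 200 mW, and the best power at that dose. The claim is about a joint optimum. The two agree for certain only under a condition that the article does not mention. A dose dropped after phase 1 is never tried at another power, so no later analysis can recover it.

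The second issue is the range. Under a biphasic response, a level is shown to be an optimum only when something lower and something higher both do worse. For some possible winners the design has no such comparison on one side.

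What is at stake is the trial's main message. One dose-power pair could be reported as ideal when the data show only that it was the best of a few settings, possibly at the end of the range. This holds even if the phase 1 pick is correct.

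**Working it through.** **Inputs.** Doses of 2, 6 and 10 J per diode plus 0 J, all at 200 mW (Variation of dose). Powers of 100, 200 and 400 mW plus 0 mW, at one dose (Variation of power). Energy E = power P × time t (same section).

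**1. The article's own times.** With t = E/P, 10 J needs 10/0.1 = 100 s, 10/0.2 = 50 s and 10/0.4 = 25 s. Phase 1 at 200 mW needs 2/0.2 = 10 s, 6/0.2 = 30 s and 10/0.2 = 50 s. All agree with the article. Its arithmetic is sound, and in phase 1 dose and irradiation time are one and the same variable.

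**2. Coverage.** The same formula fills the grid:

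| Dose per diode | 100 mW | 200 mW | 400 mW |
|---|---|---|---|
| 2 J | 20 s | 10 s | 5 s |
| 6 J | 60 s | 30 s | 15 s |
| 10 J | 100 s | 50 s | 25 s |

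There are 3 × 3 = 9 active combinations. Phase 1 tests the 200 mW column (3). Phase 2 tests one row (3), of which the 200 mW cell is a repeat. Tested: 3 + 3 − 1 = 5. Never tested: 9 − 5 = 4, namely the two dropped doses at 100 and 400 mW.

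**3. When the search is sure to succeed.** Ignore sampling error. Phase 1 picks the row with the best value in the 200 mW column; phase 2 then searches that whole row. The best of the nine is reached exactly when its row is also the best row at 200 mW. Additive dose and power effects guarantee this. They are not required: in an assumed extreme case with nine unrelated cell means, the best cell lies in the 200 mW column with chance 1/3 and is then found; otherwise (2/3) its row is picked with chance 1/3. The total is 1/3 + 2/3 × 1/3 = 5/9, or 56%. A simulation of 200,000 runs also gave 56%, and 100% under additivity. These figures show how much rests on the condition; they are not estimates for this trial.

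**4. How the condition could fail (assumed example).** Suppose some minimum exposure between 10 and 20 s is needed. Then 2 J at 200 mW (10 s) fails and is dropped, while 2 J at 100 mW (20 s) would pass the threshold but is never tested. The article gives no such threshold.

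**5. Bracketing, winner by winner.**

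| Winner | Lower level tested | Higher level tested | Bracketed if both do worse |
|---|---|---|---|
| 2 J | 0 J | 6 J | yes |
| 6 J | 2 J | 10 J | yes |
| 10 J | 6 J | none | no |
| 100 mW | none at that dose | 200 mW | no |
| 200 mW | 100 mW | 400 mW | yes |
| 400 mW | 200 mW | none | no |

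The 0 J group is a true lower dose. The 0 mW group is not a lower power at the same dose, because it delivers no energy.

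**6. What each phase 2 result supports.** If 200 mW wins, the pair has been compared with the other doses at its power and the other powers at its dose; four combinations stay unknown. If 100 or 400 mW wins, the dose was chosen at a different power and no dose comparison exists at the winning one.

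**The case against.** The strongest reply is that a two-step search is a legitimate economy. A full 3 × 3 grid plus placebo at 7 per group would need 10 × 7 = 70 athletes, against 28 per phase (56 places over both phases). The levels and their order are openly stated, the link between dose and time is disclosed, and the Discussion later speaks of an intention to find ideal parameters. Earlier work, not available here, may justify the range. This stands as a defence of the design. It does not defend a conclusion stated without limits.

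Three stronger readings are tempting, and the documents do not support them:

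- A reader might infer that the search works only if dose and power act independently. Independence is sufficient, not necessary (step 3).
- A reader might infer that the Discussion itself says the best dose depends on power. It says that irradiation time and power can each matter, which is the reason for phase 2. That leaves an interaction open without showing one.
- A reader might infer that only the middle level of each phase can be an optimum. For dose this is wrong: a 2 J winner that beats both 0 J and 6 J has a worse level on each side, and such a rise and fall would fit the biphasic pattern.

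Nor can a probability be put on an unbracketed result, since the article gives no basis for how likely each level is to win.

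**Conclusion.** The point holds as a mismatch between the stated conclusion and the design. The design can show the best of three doses at 200 mW and the best of three powers at the chosen dose. It tests 5 of 9 active combinations and cannot, in general, identify the ideal pair. The count follows from the stated design alone. That the best pair might be missed depends on an interaction that the article neither shows nor rules out. The bracketing gap concerns three possible winners: 10 J, 100 mW and 400 mW. An analysis plan cannot close either gap, because the missing settings yield no data. The two-step design itself is not at fault.

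**What to change.** Restate the conclusion in three places: the aim in the abstract, the opening of Variation of power (phase 2), and the first sentence of the Discussion. Suggested wording: *the best of 2, 6 and 10 J at 200 mW (dose and irradiation time vary together), and the best of 100, 200 and 400 mW at that dose.*

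Add one reading rule: *A level is called an optimum within the tested range only if a tested lower level and a tested higher level both do worse; for dose, 0 J counts as a lower level. If 10 J, 100 mW or 400 mW wins, the report states that the optimum is not bracketed by the tested range.*

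The cost is a less ambitious claim. Arms, doses and sample size stay as they are. Trial status says volunteers were being recruited at submission, so the rule should be fixed before any results are seen.
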